## 1. List of abbreviations

| CHD | Chronic Heart Disease |
| --- | --- |
| CI | Confidence Interval |
| DMC | Data Monitoring Committee |
| EQ5D-5L | EuroQol 5D -5 Long |
| FOCUS | Fluoxetine Or Control Under Supervision |
| GI | Gastrointestinal |
| HRQOL | Health Related Quality of Life |
| MHI5 | Mental Health Inventory 5 |
| mRS | Modified Rankin Score |
| NIHSS | National Institute of Health Stroke Score |
| OCSP | Oxford Community Stroke Project |
| SF-36 | Short Form-36 |
| SIS | Stroke Impact Scale |
| SSV | Six Simple variable |
| TIA | Transient Ischaemic Attack |
| TSC | Trial Steering Committee |
|  |  |
|  |  |

## 2. Introduction

Fluoxetine Or Control Under Supervision (FOCUS) is a parallel-group multicentre randomised trial to establish the effect(s) of routine administration of Fluoxetine in patients with a recent stroke. The trial aims to recruit at least 3000 patients. Patients are randomised via a web based randomisation system utilising a minimisation algorithm with a random component to receive Fluoxetine 20mg once daily or matching placebo capsules for 6 months and follow up at 6 and 12 months.

## 3. Statistical methods from protocol

Our primary analyses will retain patients in their original assigned treatment groups.

Our primary analysis will compare the mRS at the six month follow up using an ordinal analysis adjusted for any baseline imbalance in those factors included in our minimisation algorithm.

We will compare the mRS at the twelve month follow up to establish if any benefits observed at 6 months are maintained.

Secondary analyses will compare the two treatment groups with respect to the following outcomes at 6 and 12 months.

- Survival (Logistic regression)
- EQ5D-5L (HRQOL) to generate utilities
- SIS (for each of 9 domains on which the patient scored 0-100)
- MHI 5 (mood)
- Fatigue (Vitality subscale of SF36)
- New diagnosis of depression requiring treatment with antidepressants
- Adverse events
- Adherence to trial medication

Longer term survival will be analysed with Cox proportional hazards model

We will also perform analyses of potential mediating factors e.g. the role of depression. We will seek to answer the question whether any benefits are mediated by improvement in mood (based on MHI 5 and also whether any apparent loss of benefits in mRS or SIS between 6 months to 12 months is because of a deterioration in mood.

**Pre-defined subgroups**

The mRS will be compared at six months with an ordinal analysis in the following subgroups:

- Age (≤70, > 70yrs)
- Baseline probability of a good outcome on mRS (Counsell 2002) – to see if effects remain constant across the range of stroke severities (<0.15 vs 0.15-1 probability of being alive and independent at 6 months)
- Ischaemic vs haemorrhagic stroke
- Patient who were unable to consent for themselves since this subgroup will allow us to answer the question whether routine use of fluoxetine is likely to benefit patient in whom a formal assessment of mood is impossible because of communication and cognitive problems.

In addition we are particularly interested to know whether the effect of treatment on neurological function is modified by specific neurological deficits present at baseline. Because patients may have a combination of neurological deficits, individual patients may appear in more than one subgroup

Patients with a motor deficit (i.e. weakness or clumsiness on NIHSSS) affecting face, arm or leg.

- Relevant outcomes – SIS – Strength, mobility, hand/arm function
- Patients with aphasia based on the NIHSS
- Relevant outcomes – SIS - communication

## 4. Study Methods

### 4.1. Randomisation and blinding

Having obtained consent, the randomising person collects the baseline data necessary to complete a randomisation form and enters the patient’s baseline data into our computerized central randomisation service by means of a secure 24/7 Web interface or a telephone call to the trial office during office hours. After the computer program has checked these baseline data for completeness and consistency it allocates that patient a unique study identification number and a treatment pack number which corresponds to either Fluoxetine or Placebo. The system applies a minimisation program to achieve balance for four factors:

- Delay since stroke onset [2 – 8 days v 9 – 15 days]
- Predicted outcome at 6 months based on Counsell 2002 [predicted probability of being alive & independent at 6 months of 0 – 0.15 v 0.16 – 1]
- Presence of a motor deficit [yes v no – where deficit is NIHSS5 (right or left) >0, NIHSS6 (right or left)>0 or NIHSS7 >0]
- Presence of aphasia [NIHSS question 9: 0 v 1 – 3 ]

The minimisation algorithm randomly allocates the first patient to a treatment, but allocates each subsequent patient to the treatment that leads to the least difference between the treatment groups with respect to the prognostic factors (Altman 2005). To ensure that we retain a random element to treatment allocation, patients will be allocated to the group which minimizes differences between groups with a probability of 0.8. The system contains a list of treatment codes for each centre and which match the stocks held at that centre. At the end of the session each patient is allocated a treatment code which corresponds to either an active (f.luoxetine 20mg once daily) or placebo treatment pack which contains six months supply of capsules held at that centre. The randomisation system will take account of the drug stocks held locally to firstly ensure the allocated treatment is available and second to minimise wastage.

The patient, their families, the healthcare team including the pharmacist and anyone involved in outpatient assessments will be blinded to the treatment allocation.

### 4.2. Study Assessments

|  | Days | Weeks | | | | | | | |
| --- | --- | --- | --- | --- | --- | --- | --- | --- | --- |
| **Assessment** | 2-15 | 4-6 | 12 | 24 | 26 | 30 | 50 | 52 | 54 |
| ***Local*** |  |  |  |  |  |  |  |  |  |
| Screen of eligibility | x |  |  |  |  |  |  |  |  |
| Check results of post stroke bloods | x |  |  |  |  |  |  |  |  |
| Give PIB to patient and/or carer | x |  |  |  |  |  |  |  |  |
| CONSENT | x |  |  |  |  |  |  |  |  |
| Collect baseline data | x |  |  |  |  |  |  |  |  |
| Randomise | x |  |  |  |  |  |  |  |  |
| Record treatment code/study no. | x |  |  |  |  |  |  |  |  |
| Prescribe study medication | x |  |  |  |  |  |  |  |  |
| Dispense 6 months of treatment | x |  |  |  |  |  |  |  |  |
| FAX no. of dispensed medication | x |  |  |  |  |  |  |  |  |
| Complete discharge form including |  | + |  |  |  |  |  |  |  |
| Adverse events |  | + |  |  |  |  |  |  |  |
| All medications |  | + |  |  |  |  |  |  |  |
| Adherence |  | + |  |  |  |  |  |  |  |
| Updated contact details |  | + |  |  |  |  |  |  |  |
| ***Central (postal or telephone)*** |  |  |  |  |  |  |  |  |  |
| Email/fax notification of allocation | x |  |  |  |  |  |  |  |  |
| Letter informing GP of participation | x |  |  |  |  |  |  |  |  |
| 1 month follow up for outpatients |  | o |  |  |  |  |  |  |  |
| 3 month prompt to patients |  |  | x |  |  |  |  |  |  |
| GP Questionnaire |  |  |  | x |  |  | x |  |  |
| Adverse events |  | o |  | x |  |  |  |  |  |
| Follow up on previous AEs |  |  |  | x |  |  | x |  |  |
| All medications |  | o |  | x |  |  | x |  |  |
| Adherence |  | o |  | x |  |  |  |  |  |
| Resource use |  |  |  | x |  |  | x |  |  |
| Patient follow up |  |  |  |  |  |  |  |  |  |
| Adverse events |  | o |  |  | x |  |  |  |  |
| Follow up on previous AEs |  |  |  |  | x |  |  | x |  |
| Adherence |  | o |  |  | x |  |  |  |  |
| modified Rankin scale |  |  |  |  | x |  |  | x |  |
| Stroke Impact Scale |  |  |  |  | x |  |  | x |  |
| Mental health inventory 5 |  |  |  |  | x |  |  | x |  |
| EQ5D-5L (HRQOL) |  |  |  |  | x |  |  | x |  |
| SF36 Vitality subscale |  |  |  |  | x |  |  | x |  |
| Resource use |  |  |  |  | x |  |  | x |  |
| Retrieve residual capsules (pill count, reconciliation and destruction) |  |  |  |  | x |  |  |  |  |

+ - only for patients enrolled as inpatients

o - only for patients enrolled as outpatients

### 4.3.1. Stroke Impact Scale [SIS]

The SIS [version 3] is 59 questions broken into 8 domains which are scored by calculating the transformed scale using the formula:

Transformed scale = [(raw score – lowest possible raw score)/possible raw score range] * 100

***I have found things which give the formula above but Im not sure if any of the questions are inverted and would good to see what the produces of scale say about calculating the score if someone has missed out a question[s].***

### 4.3.2. Mental Health Inventory 5 [MHI-5]

MHI-5 results in a score from a minimum of 5 to a maximum of 30, a higher score indicating psychological well-being and the absence of psychological distress during the past month.

To obtain the total score responses to all 5 questions are assigned a score and then summed across all questions. For questions 1 and 2 these are scored 1 point for ‘all of the time’ through to 6 points for ‘none of the time’ and for questions 3, 4 and 5 6 points are allocated for ‘all of the time’ or ‘always’ through to 1 point for ‘none of the time’ or ‘never’.

Source: <http://www.prisonmentalhealth.org/page_view.asp?c=10&did=915&fc=001007004>

### 4.3.3. EuroQol 5D-5L [EQ5D-5L]

EQ5D-5L gives a numerical value to the ‘health state’ of a person. The EQ5D-5L consists of five dimensions, each with five levels of perceived problems:

Level 1: no problem

Level 2: slight problems

Level 3: moderate problems

Level 4: severe problems

Level 5: extreme problems

Each level is assigned a numerical code [level 1 = code 1, level 2 = code 2, etc]. These dimensions are combined to give a 5 digit code with any missing dimension coded as ‘9’. Using this code we can then convert to a single index value.

EQ5D has recently been updated from 3L to 5L and at this time the producers of the measure don’t have sufficient study data to produce indexes directly so are using the ‘Crosswalk value set for EQ5D-5L’ which extrapolates from the 3L to the 5L. We expect this will be superseded with country specific values based on test data but this may take some time and may or may not be available at any point during this trial. We will use the most up to date set of index coding for this instrument at the time of analysis [http://www.euroqol.org/about-eq-5d/valuation-of-eq-5d/eq-5d-5l-value-sets.html].

Source: <http://www.euroqol.org/fileadmin/user_upload/Documenten/PDF/Folders_Flyers/UserGuide_EQ-5D-5L.pdf>

### 4.3.4. Short Form 36 [SF36] Vitality

SF36 [version 2] uses responses from 36 questions to score 8 domains, in this trial we are interested only in the vitality domain. In the full SF-36 the vitality questions are 9a, 9e, 9g, 9i. For a & e these are scored 5 points for ‘all of the time’ through to 1 point for ‘none of the time’ while g & i are scored 1 point for ‘all of the time’ through to 5 points for ‘none of the time’. A raw score is then calculated by summing across the four questions, resulting in a score from 4 to 20 with a range of 16. The raw scores are then transformed to a score ranging from 0 to 100 using the formula:

Transformed scale = [(raw score – lowest possible raw score) / possible raw score range] * 100

Source: Ware JE, Kosinski M, Dewney JE. How to Score Version 2 of the SF36 Health Survey. Lincoln, RI. Quality Metric Incorporated, 2000.

### 4.3.5. National Institute of Health Stroke Score [NIHSS]

The NIHSS is a 15 item questionnaire where responses to each question are assigned a score from 0 to 4 [some questions are scored 0 to 2 or 0 to 3 as appropriate]. The total score is calculated by summing across all questions.

### 4.3.6. Six Simple variable (SSV) model

Based on the work ‘C.Counsell, M.Dennis, M.McDowall,C.Warlow. Validation of New Prognostic Models Predicting Outcome After Acute and Subacute Stroke : Development and Validation of New Prognostic Models. *Stroke* 2002, 33:1041-1047’ we can calculate the probability of being alive and independent at 6-months using the following model:

[figure not shown]

### 4.3.7. Modified Rankin Score [mRS]

The simplified version of the Modified Rankin score is based on the yes/no responses to 5 questions and is scored as follows:

[figure not shown]

Source: Bruno A, Akinwuntan AE, Lin C, Close B, Davis K, Baute V, Aryal T, Brooks D, Hess DC, Switzer JA, Nichols FT. Simplified modified rankin scale questionnaire: reproducibility over the telephone and validation with quality of life. Stroke. 2011 Aug;42(8):2276-9

## 5. General Considerations

### 5.1. Overall

For all analyses, unless otherwise specified, we will retain participants in the treatment group to which they were originally assigned, irrespective of the treatment they actually received.

### 5.1.1. Timing of Final Analysis

The final analysis will be performed after the required number of patients has been recruited and followed up to a minimum of 12 months post recruitment. The final analysis will be performed on the data set after any ‘cleaning’ that may be required has been completed and the database locked.

### 5.1.3. Missing Data

mRS includes death so it is expected that the number with missing mRS at follow up will be minimal. Anyone with missing mRS will not be included in any analysis requiring mRS (complete case analysis).

For the quality of life measures [SF-36, EQ5D, MHI-5, SIS] we will present results for those who are alive at follow up and any discrepancy in death rates between groups will be taking into account in the interpretation. Missing data for single questions within scores will handled as detailed by each scoring method, where responses to all questions within a scale are missing that patient will not be included in that part of the analysis. If required due to amount of patients with missing scores a sensitivity analysis may be performed.

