### 7.2. Secondary outcomes - binary

Where the outcome of interest is binary, comparison by treatment group will be examined using a binary logistic regression and will be adjusted for factors used in the minimisation algorithm, unadjusted odds ratios will also be presented. In addition the results will be presented as relative risks with 95% CI, calculated from the odds ratio [using methods described by Deeks JJ, Higgins JPT, Altman DG (editors). Chapter 9: Analysing data and undertaking meta-analyses. In: Higgins JPT, Green S (editors). Cochrane Handbook for Systematic Reviews of Interventions. Version 5.0.1 [updated September 2008]. The Cochrane Collaboration, 2008. Available from [www.cochrane-handbook.org](http://www.cochrane-handbook.org/).] and absolute risk differences with 95% CI.

1. Modified Rankin score at six-months [mRS 0-2 v mRS 3-6].
2. Death from any cause by six-months.
3. Death from any cause by twelve-months.
4. New diagnosis of depression since randomisation by six-months.
5. New diagnosis of depression since randomisation by twelve-months.

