### 7.4. Secondary outcomes - continuous

Where the outcome of interest is continuous, these will be compared between treatment groups using linear regression adjusting for factors in the baseline minimisation, or an alternative approach as necessary. This analysis will be conducted for the following outcomes at both six and twelve months.

1. Quality of life as measured by the EuroQol [EQ-5D]
2. Depression and anxiety as measured by the mental health inventory 5 [MHI-5 – question 21,22 of 6-month follow up; question 17,18 of 12-month follow up] and SIS [question 14 on 6-month follow up; question 10 on 12-month follow up].
3. Fatigue as measured by the vitality sub-scale of the Short Form (36) Health Survey [SF-36 question 20 on 6-month follow up; question 16 on 12-month follow up].
4. Limb strength as measured by SIS [question 12 on 6-month follow up; question 8 on 12-month follow up].
5. Hand function as measured by SIS [question 18 on 6-month follow up; question 14 on 12-month follow up].
6. Cognitive function as measured by SIS [question 13 on 6-month follow up; question 9 on 12-month follow up].
7. Communication as measured by SIS [question 15 on 6-month follow up; question 11 on 12-month follow up].
8. Extended ADL as measured by SIS [question 16 on 6-month follow up; question 12 on 12-month follow up].
9. Mobility as measured by SIS [question 17 on 6-month follow up; question 13 on 12-month follow up].
10. Social activity as measured by SIS [question 19 on 6-month follow up; question 15 on 12-month follow up].
11. Overall patient outcome as measured by the SIS total score
12. Overall recovery as measured by SIS thermometer [question 28 on 6-month follow up; question 24 on 12-month follow up].

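### EQ-5D is compared in survivors only, so any effect of fluoxetine on mortality would distort the comparison, and no planned analysis measures by how much

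*SAP*

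**What the plan says.** SAP section 5.1.3 limits SF-36, EQ-5D, MHI-5 and SIS to survivors: "we will present results for those who are alive at follow up". The same sentence adds that "any discrepancy in death rates between groups will be taking into account in the interpretation". It names no method for doing so. A patient with no responses at all on a scale is left out of that part of the analysis. The only sensitivity analysis mentioned is optional and depends on missing scores, not on deaths: "If required due to amount of patients with missing scores a sensitivity analysis may be performed".

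Section 3 lists EQ-5D among the outcomes at 6 and 12 months as "EQ5D-5L (HRQOL) to generate utilities", and section 4.3.3 converts the five-digit code to a single index value. Section 7.4 puts EQ-5D first of twelve continuous outcomes, to be "compared between treatment groups using linear regression adjusting for factors in the baseline minimisation, or an alternative approach as necessary". None of these sections gives a value for death.

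The primary outcome is treated differently: section 5.1.3 notes that "mRS includes death so it is expected that the number with missing mRS at follow up will be minimal". Mortality is analysed separately in section 7.2 ("Death from any cause by six-months", and again at twelve months) and by a Cox model in section 7.5.

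**The concern.** Survival to follow-up happens after randomisation. If treatment affects it, comparing EQ-5D among survivors is no longer a comparison of the randomised groups. Suppose fluoxetine keeps alive some severely disabled patients who would have died on placebo. They enter the treated survivors with low utilities and pull that arm's mean down, although no patient is worse off in quality of life for having been treated. The reverse also holds: a treatment that increased deaths among such patients would seem to improve quality of life.

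A promise to allow for unequal deaths in the interpretation changes no estimate and names no threshold. A reader facing unequal deaths could not tell from the planned output how much of an EQ-5D difference came from who survived. A mortality effect is not a remote possibility on the plan's own terms. Death is a secondary outcome, section 5.2.1 gives it as an example of a major event for stopping, and section 4.1 minimises on a stratum with a predicted probability of 0 to 0.15 of being alive and independent.

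**Working it through.** The SAP states no death rate, utility or SD, so there is no figure of its own to reproduce.

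**Inputs**
- From the SAP: at least 3000 patients (section 2).
- Assumed: 1:1 allocation, hence 1500 per arm; control survivor mean utility m = 0.55; SD 0.30; death scored 0; all survivors respond (relaxed in step 4).
- Assumed: the only effect of treatment is to prevent a share dC - dT of deaths, and the patients saved have utility u.

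**Step 1. Formulas**
- Survivor-only difference = (dC - dT)(u - m)/(1 - dT)
- All-randomised difference with death scored 0 = (dC - dT)u
- SE of the survivor difference = SD × sqrt(1/[1500(1 - dC)] + 1/[1500(1 - dT)])
- Chance of a significant apparent harm = Φ(-1.96 - z), where z = difference/SE

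**Step 2. Deaths 10% v 8%**
- SE = 0.30 × sqrt(1/1350 + 1/1380) = 0.0115
- u = 0: 0.02 × (-0.55)/0.92 = -0.0120; z = -1.04; chance 0.18; death-as-0 difference 0
- u = 0.2: 0.02 × (-0.35)/0.92 = -0.0076; z = -0.66; chance 0.10; death-as-0 difference +0.004

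**Step 3. Other death rates, at u = 0.1**

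| Deaths, control v fluoxetine | Survivor-only difference | SE | Chance of significant harm | Death-as-0 difference |
| --- | --- | --- | --- | --- |
| 10% v 10% | 0 | 0.0115 | 0.025 | 0 |
| 10% v 9% | -0.0049 | 0.0115 | 0.06 | +0.0010 |
| 10% v 8% | -0.0098 | 0.0115 | 0.13 | +0.0020 |
| 15% v 12% | -0.0153 | 0.0118 | 0.26 | +0.0030 |
| 20% v 15% | -0.0265 | 0.0121 | 0.59 | +0.0050 |

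For SD 0.25 to 0.35, the chance at 10% v 8% is 0.17 to 0.11, and at 20% v 15% it is 0.75 to 0.47.

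The two differences have opposite signs only when 0 < u < m. At u = 0 the death-as-0 difference is nil. At u = -0.1 both are negative (10% v 8%: -0.0141 and -0.0020).

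**Step 4. What happens if deaths are scored 0 and living non-responders are simply dropped**

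Assume 80% of survivors respond in both arms, with deaths at 10% v 8%. All deaths are counted but only 80% of survivors, so deaths are over-weighted.
- Control: 0.8 × 0.90 × 0.55/(0.8 × 0.90 + 0.10) = 0.396/0.820 = 0.4829
- Fluoxetine, u = 0: 0.396/(0.8 × 0.92 + 0.08) = 0.396/0.816 = 0.4853
- Difference +0.0024, where the true value is 0. For u = 0.1 it is +0.0043 (true +0.0020), and for u = 0.2 it is +0.0063 (true +0.0040).

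The companion analysis therefore has to deal with living non-responders explicitly.

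**The case against.** The plan sees the problem and says so. Deaths by arm are already analysed at 6 and 12 months and by Cox model, and the primary mRS carries death as its worst category, so EQ-5D would not be read without them. Quality of life among the living, reported beside mortality, answers an intelligible question. EQ-5D is secondary, every input above except the total sample size is assumed, and a benefit in other survivors could offset the artefact. The companion analysis would also have little power. At 10% v 8% its effect is at most +0.004. The composite SD is about sqrt(0.9 × 0.30² + 0.9 × 0.1 × 0.55²) = 0.33, so its SE is about 0.33 × sqrt(2/1500) = 0.012 and z is about 0.33.

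All of this limits the weight of the point without answering it. Mortality results show that deaths differ, but they do not show what that does to the EQ-5D difference. The companion analysis is there to show whether an apparent harm persists once deaths are counted, and it does not need to be significant to do that.

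Three stronger readings are tempting and are not supported:
- A reader might infer that a treatment which saves severely disabled patients is bound to look harmful. At a 2-point mortality reduction there is an 82-90% chance of no significant harm, and strict sign reversal needs 0 < u < m.
- A reader might infer that scoring death 0 lets everyone with known vital status be included. It adds only the deaths; a living patient who returns no EQ-5D still has no utility.
- A reader might infer that the plan overlooks mortality. Section 5.1.3 shows otherwise; what it lacks is an analysis.

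**Conclusion.** The point holds in a conditional form. If fluoxetine changes mortality, the planned EQ-5D comparison is confounded by who survives, and nothing in the SAP measures the distortion. Under the stated assumptions, a 2-point reduction in deaths produces an artefact of about 0.7 to 1.0 SE. A 1-point reduction produces less (0.43 SE at u = 0.1), and a 5-point reduction from 20% could by itself make a significant apparent harm more likely than not. With no mortality effect and no change in who dies, the artefact is zero. The primary analysis is unaffected because the mRS includes death. This is a worthwhile, inexpensive improvement to a secondary outcome. The value of 0 for death is a utility convention and does not come from the SAP.

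**What to change.** Keep the survivor analysis. In sections 5.1.3 and 7.4, pre-specify a companion analysis of the EQ-5D utility at 6 and 12 months:
- State that death by the time of the assessment is scored 0.
- Use the same linear model adjusted for the minimisation factors, with robust standard errors.
- Treat living non-responders separately from deaths, by multiple imputation or by inverse-probability-of-response weighting among survivors, so that deaths are not over-weighted.
- Present both results side by side, with the number of deaths in each arm.

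The cost is one additional analysis per visit, plus the imputation or weighting model, which should be fixed before unblinded data are seen. The downsides are that the composite mixes mortality with quality of life, which is why both results are shown, and that it relies on a missing-at-random assumption for living non-responders.
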